## Abstract

**Background:**

HIV incidence in adolescent girls and young women remains high in sub-Saharan Africa. Progress towards uptake of HIV prevention methods remains low. Studies of oral pre-exposure prophylaxis (PrEP) have shown that uptake and adherence may be low due to low-risk perception and ambivalence around using antiretrovirals for prevention. No evidence exists on whether an interactive intervention aimed at adjusting risk perception and addressing the uncertainty around PrEP will improve uptake. This pilot research trial aims to provide an initial evaluation of the impact of an interactive digital tablet-based counselling session, correcting risk perception, and addressing ambiguity around availability, usability, and effectiveness of PrEP.

**Methods/Design:**

This is a matched-cluster randomized controlled trial which will compare an interactive tablet-based education intervention against a control with no intervention. The study will be implemented in eight sites. In each site, two matched clusters of villages will be created. One cluster will be randomly allocated to intervention. In two sites, a community engagement intervention will also be implemented to address social obstacles and to increase support from peers, families, and social structures. A total of 1200 HIV-negative young women aged 18–24 years, not on PrEP at baseline, will be eligible. Baseline measures of endpoints will be gathered in surveys. Follow-up assessment at six months will include biomarkers of PrEP uptake and surveys.

**Discussion:**

This will be the first randomized controlled trial to determine whether interactive feedback counselling leads to uptake of HIV prevention methods such as PrEP and reduces risky sexual behavior. If successful, policymakers could consider such an intervention in school-based education campaigns or as post-HIV-testing counselling for young people.

**Trial registration:**

Clinicaltrials.gov, NCT03565575. Registered on 21 June 2018.

## Background

HIV incidence remains extremely high in adolescent girls and young women (AGYW) aged 15–24 years in sub-Saharan Africa, accounting for one in five new HIV infections in 2017 despite representing just 10% of the population [1]. The urgency to reduce HIV incidence among AGYW is widely recognized. The United Nations General Assembly adopted a Political Declaration with the target of < 100,000 new infections in AGYW by 2020 [2]. In Zimbabwe, where 9000 AGYW became newly infected with HIV in 2017, the Zimbabwe National HIV and AIDS Strategic Plan aims to halve HIV incidence by 2020 [3].

A number of efficacious HIV prevention methods exist that could reduce HIV incidence for AGYW either directly (e.g. pre-exposure prophylaxis [PrEP], condoms, partner reduction) and indirectly (e.g. male partner reduction, voluntary medical male circumcision [VMMC]) but use of these strategies is still low [4]. PrEP, in particular, can empower individuals with few other personal prevention options and so has the potential to strongly reduce HIV incidence among AGYW [5, 6]. However, PrEP remains largely unavailable in sub-Saharan Africa and slow progress has been made towards the UNAIDS 2020 target of reaching 3 million people at risk of HIV with PrEP [5].

Oral PrEP has demonstrated substantial HIV prevention benefits (up to 75% reduction in HIV incidence) in trials. Qualitative evidence from the VOICE trial indicates that low uptake and adherence may be due to uncertainty and ambivalence about using antiretrovirals for prevention and concerns about side effects [7]. In addition, the FEM-PrEP study found that women underestimated their risk of infection and that perceived risk was associated with greater adherence to PrEP [8]. A key gap is whether, when counselled about their risk of infection, the local availability, effectiveness, tolerability, and ease of use of PrEP, AGYW in Zimbabwe will take up oral PrEP.

Two previous studies have evaluated the impact of disaggregated information on HIV risks. Datta et al. [9] evaluated the impact of an interactive computer game on changes in respondents’ (men and women aged 15–19 years) understanding of the relationship between HIV-risk and age, and retention of knowledge after three months. Dupas [10] evaluated a classroom intervention (women in grade 8) providing disaggregated risk information to young women and used teen pregnancies as an objective proxy for unprotected sex. These studies, however, did not consider long-term behavior change, for example, partner reduction or uptake of HIV prevention methods. In the case of Datta and Burns [9], the sample consisted of university students so may be of limited generalizability.

The present study makes several innovative contributions. It tests the usability and acceptability of interactive learning delivered through tablets in urban and rural populations in a sub-Saharan African setting. In addition, it is the first study to evaluate longer-term behavior change resulting from interactive feedback-based learning regarding relative HIV risk. It evaluates the impact of such learning on uptake of PrEP, a relatively new HIV prevention method in Africa.

The purpose of this study is to pilot test and evaluate the impact on risk perception and PrEP uptake within six months in AGYW aged 18–24 years of an interactive digital tablet-based counselling session, aiming at correcting risk perception and addressing ambiguity around availability, usability, and effectiveness of PrEP. The study hypothesizes that correcting misperceptions of risks of HIV infection and offsetting ambiguity effects about the availability, usability, and efficacy of PrEP, through localized, interactive, tablet-based counselling, will improve risk perception and increase uptake of PrEP in HIV-negative AGYW without having an adverse effect on underlying sexual risk behavior.

## Methods/Design

### Study design

This is a prospectively registered, two-arm matched-cluster randomized controlled trial (RCT) with single (outcomes assessor) masking, intention-to-treat analysis, and six-month follow-up (Fig. 1). The study is being implemented in eight sites in Manicaland Province, east Zimbabwe. The study will be implemented consecutively on a site-by-site basis. In each site, two matched clusters of villages will be created. Clusters will be randomly allocated to intervention or control arm. In each study site, a census of all households in the study clusters at baseline will be used to identify AGYW aged 15–24 years who are resident within the study areas. A detailed individual questionnaire will collect information on primary endpoints, following which provider-initiated HIV testing and counselling will be offered. Individuals identified as eligible following this stage will be invited to participate in the intervention.

**Fig. 1 Fig1:**
[figure not shown]
Study design

Intervention participants will play an interactive digital tablet-based quiz including the following information components: (1) risks of HIV infection under different scenarios such as between two hypothetical individuals and with different behaviors; and (2) interactive counselling on key facts around PrEP, its usability, and local availability. Participants will have the option to sign up for contact by a nurse from the health clinic to discuss PrEP further and to make an appointment for a visit. In addition, in two of the eight sites, a community-engagement intervention using Community Conversations (CC) [11, 12] will be implemented to address social and cultural barriers to taking up PrEP and support the abovementioned individual-level intervention. No interventions will be implemented in the control arm.

Participant informed consent and data collection will be carried out by trained research assistants. HIV testing will be done by appropriately trained and accredited staff following the standard procedures and testing algorithm used in the Zimbabwe Ministry of Health and Child Care (ZMoHCC) routine provider-initiated testing and counselling (PITC) services. HIV field test results will be returned to participants the same day. Participants who test positive for HIV will receive referral to treatment services in accordance with national guidelines. Participants testing negative for HIV will also receive post-test counselling and, in intervention clusters, will be invited to participate in the intervention.

Intervention participants will be referred to clinics offering PrEP. When individuals begin PrEP in the form of Truvada (a fixed combination of Tenofovir-TFV and Emtricitabine-FTC), adherence to the once-daily intake of the drug will be monitored using the levels of TFV as a biomarker [13]. This will give direct quantitative measures of adherence and will enable appropriate interventions to be implemented to reduce both the risk of sero-conversion and the risk of developing drug resistance to the acquired infection. Dried blood spots (DBS) will be collected from participants six months after initiation of Truvada-based PrEP.

Statistical analyses will be carried out by researchers blinded to group allocation. Before enrolment, all participants will provide written informed consent. All personal data will be confidential. The study has obtained ethical approvals from the Medical Research Council of Zimbabwe (Ref. MRCZ/A/2243), the institutional review board of the Biomedical Research and Training Institute in Zimbabwe (Ref. AP140/2017), and the Imperial College London Research Ethics Committee (Ref. 17IC4160).

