
### Inclusion and exclusion criteria

A total of 1200 women will be considered eligible if: (1) they are aged 18–24 years; (2) they live in the intervention cluster (see below) in one of the eight study sites in Manicaland province; and (3) they expect to be resident there for the duration of the study. Participants will be excluded if they test positive for HIV at baseline or self-report taking PrEP at baseline. To avoid indirect disclosure of the status of HIV-positive individuals, a random sample of 90% of otherwise eligible HIV-negative women will be selected to participate in the intervention.

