### Randomization/masking

In each study site, community leaders will first be contacted and clearance will be sought to carry out activities. In addition, community meetings will be organized to introduce the activities before the start of any procedures. Within each of the eight study sites (including the two sites with the additional CC intervention component), detailed site maps will be used to create two matched clusters of villages based on socioeconomic characteristics and factors such as distances to trading centers, major roads, and health centers. Clusters within a site will be randomly allocated to intervention or control using a simple coin toss process. Thus, all eight sites will contain two clusters each (intervention and control). Young women in intervention clusters will receive the interactive intervention (and in two sites, CCs will also be implemented). Young women in the control villages will receive no intervention and will be followed up for measurement of outcomes at six months. Participants will not be masked for the intervention they receive due to cluster level randomization and the nature of the intervention. Study interventions and measurements will occur in separate locations and time points thus facilitating the blinding of outcomes assessors.

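### As the steps are ordered, clusters are allocated before women are enrolled and nothing conceals the arm, so consent and self-reported baseline answers can be given with the arm known

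*Protocol article*

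**What the plan says.** All references are to the protocol article.

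- Study design puts allocation first: "Clusters will be randomly allocated to intervention or control arm". The next step is enumeration: "a census of all households in the study clusters at baseline will be used to identify AGYW aged 15–24 years". A questionnaire comes next, "following which provider-initiated HIV testing and counselling will be offered", and women found eligible are then invited.
- The same section, after Fig. 1, says of testing that "HIV field test results will be returned to participants the same day". It then makes the invitation specific to one arm: "Participants testing negative for HIV will also receive post-test counselling and, in intervention clusters, will be invited to participate in the intervention".
- Randomization/masking forms two clusters per site from site maps and continues: "Clusters within a site will be randomly allocated to intervention or control using a simple coin toss process". It does not place the toss before or after the census, consent or survey.
- Inclusion and exclusion criteria words one criterion by arm: "they live in the intervention cluster (see below) in one of the eight study sites". It also requires that women expect to stay resident, and it excludes those who test HIV-positive or report PrEP use at baseline.
- Masking is stated for outcome assessors (Study design; Randomization/masking) and for analysts (the paragraph before Qualitative explorations). Participants are stated to be unmasked.

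**The concern.** Randomising clusters protects the comparison only if participants are identified before allocation, or by people who do not know it. If the arm is known at enrolment, women interested in PrEP may be over-represented among those who consent in one arm, and the two arms then differ before any intervention is delivered. Intention-to-treat analysis, masked assessment and blinded analysis all act after enrolment and cannot repair this.

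The secondary outcomes are affected too. Risk perception is measured at baseline and at six months, and sexual behaviour is analysed as self-reported change between the two surveys. A baseline answer given with the arm known is not a clean pre-allocation value. Statistical analysis also adds as covariates any indicators unbalanced at baseline. Where those come from the same survey, the adjustment rests on data collected after allocation.

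**Working it through.** **1. Order of steps.** Study design gives: form clusters, allocate, census, questionnaire, HIV test, invitation. The account after Fig. 1 places the arm-specific invitation next to same-day results and post-test counselling. If invitations are made at that contact, the arm is known in a site once the first HIV-negative woman there is counselled. Every woman enrolled later in that site would then be recruited with the arm known, even if the toss had followed the census.

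**2. Who could know.** Research assistants take consent and collect data (Study design), and the same role explains the intervention (Intervention procedures). No sentence keeps the arm from them at enrolment. The statement that interventions and measurements are separated in place and time is offered only in support of masking outcome assessors.

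**3. What is exposed.**
- Exposed: consent, acceptance of HIV testing, expected residence, self-reported PrEP use, and baseline answers on risk perception and sexual behaviour.
- Much less exposed: the census, which covers all households, and the HIV result, which is objective.

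**4. The plan's own figures** (Sample size estimates).
- Followed-up cluster size: 600/8 = 75; 75 × 0.80 × 0.80 = 48, as stated.
- Clusters per arm for a matched design: c = 2 + (z₁₋α/₂ + z₁₋β)² × [1 + (m − 1)ICC] × [p₁(1 − p₁) + p₂(1 − p₂)] / [m(p₁ − p₂)²].
- Inputs: p₁ = 0.10, p₂ = 0.30, m = 48, ICC = 0.04, α = 0.005 taken as two-sided, power 0.80.
- Result: c = 2 + 13.31 × 2.88 × 0.30 / (48 × 0.04) = 2 + 5.99 = 7.99. That is 8 clusters, and 8 × 75 = 600 per arm.
- The stated effect of about 20% is therefore 20 percentage points. A 20% relative effect (10% v 12%) would need about 393 matched clusters per arm.
- Room for selection: at 80% consent, 600 × 0.20 = 120 eligible women per arm do not enrol.

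**5. Illustration of size.** The consent rates by interest are assumptions, not protocol figures. Let p be the share of eligible women who would take PrEP, cᵢ their consent rate, and cₙ the consent rate of the rest. Apparent uptake among those enrolled is p·cᵢ / [p·cᵢ + (1 − p)·cₙ]. Take p = 0.10 in both arms (no true effect), 80% consent for all in control, and cᵢ = 0.80 in intervention clusters.

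| cₙ in intervention clusters | Apparent uptake | Spurious difference |
|---|---|---|
| 0.80 | 0.08/0.80 = 10.0% | 0 |
| 0.70 | 0.08/0.71 = 11.3% | +1.3 points |
| 0.60 | 0.08/0.62 = 12.9% | +2.9 points |
| 0.50 | 0.08/0.53 = 15.1% | +5.1 points |

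**The case against.** The strongest reply is that the timing is inferred. No sentence dates the toss, the order in Study design is that of a summary, and the design and timeline figures are not visible here. The post-test sentence proves only that allocation is known when invitations go out. The 90% random selection of eligible HIV-negative women, the group sessions of about 20 and the separation of intervention from measurement all fit a later invitation from a list. This stands as a limit on certainty. It does not supply concealment, and the order that the article does state is the unfavourable one.

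Three other points stand:
- The community meetings are described before the toss and are not said to reveal the arm, so they are not evidence of unmasking.
- The criterion naming the intervention cluster would, read literally, bar every control woman. It looks like eligibility for the intervention or a drafting slip, and it does not date the toss.
- A woman who declines the tablet session after baseline is a non-attender. Intention-to-treat analysis handles that; it is not selection into the trial.

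A reader might infer that the toss is proven to precede consent and that everything at enrolment is open to influence. The documents do not support that. The toss date is absent, and the census and HIV result are hard to sway.

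A reader might also infer a bias of up to 10 points. That figure needs 60% overall consent in the intervention arm against 80% in control, every extra refuser a non-user, and a true uptake of 30%: 24/80 = 30% becomes 24/60 = 40%. It inflates a real effect and does not create a false one, and no consent gap of that kind is stated anywhere.

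**Conclusion.** The point holds in a limited form. As described, allocation comes before enrolment, the invitation is arm-specific in the account of post-test counselling, and nothing conceals the arm from recruiting staff or women. Consent, test acceptance, expected residence, self-reported PrEP use and the self-reported baseline measures can therefore be influenced.

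The size and direction of any bias are unknown. With no true effect, and uninterested women in intervention clusters consenting at 60–70% against 80% for everyone else, the spurious difference in uptake is about 1 to 3 points, well below the 20-point target. It would not by itself produce an effect of the size planned for. No size can be put on the secondary outcomes from the document. The case for acting is that the bias cannot be removed in analysis and the change is cheap.

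**What to change.** In each site not yet started:

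1. Complete the census, consent, baseline questionnaire and HIV testing in both clusters, with identical wording, and freeze the list of eligible women.
2. Then toss the coin, draw the 90% sample and issue invitations to the tablet sessions.
3. Date the six-month follow-up from the same point in both arms.

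Amend Study design (the order of steps and the post-test invitation) and Inclusion and exclusion criteria (the criterion worded by arm) to match. If the toss already follows baseline, no change of practice is needed; correct the stated order and say that recruiters did not know the arm.

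Cost: a short delay in each site and a separate invitation contact, which may slightly lower attendance in a population that the Discussion says may move away. The 600 per arm is unchanged. Under Trial status, recruitment began on 7 July 2018, so sites already run would have followed a different sequence. The report should state which sites used which order. Roll-out site by site makes the change practicable for the rest.

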### Qualitative explorations

Formative qualitative explorations will be embedded into different stages of the study. Formative consultations with local stakeholders and a youth advisory board will provide feedback on the intervention procedures, while qualitative studies will contextualize study outcomes by exploring local norms, experiences and perspectives concerning PrEP. Participants for the qualitative studies will be recruited from settings randomly chosen because of their rural/urban location and for being subject to both PrEP and community conversation interventions – allowing a contrast of experiences. Forty AGYW from the two settings will be invited to participate in either individual interviews (*n* = 12), focus group discussions (*n* = 18), or participatory photography (*n* = 10) with the aim of revealing how they encounter, respond to, and negotiate PrEP uptake and engagement. The AGYW will be chosen from the baseline survey by purposeful sampling following the criteria that they have to be: aged 18–24 years; HIV-negative; sexually active; considered “at risk” (according to a WHO risk screening tool); agreed to be contactable; and volunteered to participate. In addition, AGYW will be sampled to represent a mix of those who attended and did not attend PrEP sessions, to explore their reasons and motivations to participate (or otherwise) in the intervention. Individual interviews with parents of AGYW (*n* = 8), interviews with HIV prevention service providers (*n* = 12), focus groups with community members (*n* = 6; ~ 36 participants), and qualitative studies with 40 young men will also be conducted to gain insight to the broader social context of PrEP and AGYW friendly HIV-prevention services. The proposed sample sizes are estimates deemed sufficient to reach theoretical saturation [14].

### Study setting

The study is being conducted in Manicaland province in east Zimbabwe, covering an area of 36,459 km^2^ (14,077 square miles) and has a population of approximately 1.75 million (2012) (Fig. 2). Six sites enumerated in a general population cohort survey that ran from 1998 to 2013 [15]—two small towns, two large agricultural estates, and two rural villages—will be included in the study, together with two new sites in high-density urban suburbs in Mutare, the provincial capital (Fig. 2a). The total estimated population size in these areas is 35,760 people.

**Fig. 2 Fig2:**
[figure not shown]
Study sites and patterns of HIV risk in AGYW in Manicaland, Zimbabwe: (**a**) study sites by type and location; (**b**) spatial pattern of HIV prevalence, 2009–2011; (**c**) trends in HIV incidence over time, 1998–2013; and (**d**) HIV prevalence by two-year age group

Existing data show that, in the rural study sites, HIV prevalence in AGYW (15–24 years) was7.0% (20.6% in women and men aged 15–54 years) in towns and 2.1% (11.9% in women and men aged 15–54 years) in villages in 2012–2013 (Fig. 2b). Figure 2d shows prevalence increases rapidly with age. Prevalence in pregnant women (aged 15–24 years) in Sakubva, a site not previously included in the general population cohort, was 13.4% among AGYW (14.3% in women and men aged 15–54) in 2012 [16].

### Intervention procedures

At the start of the intervention, research assistants will explain the intervention to the treatment arm participants. Participants will be informed that they will be participating in an interactive tablet-based counselling quiz. The sessions will be held in groups of approximately 20 participants.

The session will begin with training on how to use the tablet and practice questions. Participants will be encouraged to ask questions by raising their hands and the research assistant will answer every question in private. Figure 3 provides an outline of the intervention procedure. Participants will then play the interactive counselling intervention. The information is primarily pictorial and all information is presented in the local language. The interactive counselling will include the following information components:
Interactive communication of the risks of HIV infection under different scenarios:
• In each round, participants will be presented with a question asking which one of two hypothetical individuals was more likely to have HIV;They will also be asked to choose between different behaviors (e.g. abstinence or condom use) to reduce the risk of acquiring HIV;Interactive counselling on key facts around PrEP including: what is PrEP; who is PrEP for; how is PrEP taken; potential side-effects; and availability.

